### **Hypothesis of the study**

There are several concepts behind this study. First the acknowledgement that imaging is playing a crucial role in the present and in the future of oncology. Secondly, we are convinced that decisions on adjuvant systemic treatment should be taken considering the biology of the disease rather than the risk of recurrence as this attitude reflects an higher probability for the patient to benefit from a certain type of treatment. Finally, a less invasive surgery associated to a more tailored medical approach is aimed at improving patients' quality of life.

The hypothesis of this trial are that:

- ✓ avoiding axillary surgery is not worsening outcome of patients with small breast cancer
- ✓ the absence of the pathological information on the risk of recurrence given by nodal status is not worsening outcome of these patients
- ✓ pre-operative imaging of the axilla can identify patients with clinically relevant nodal burden

## **TRIAL OBJECTIVES**

The aims of this prospective randomized study are:

- ✓ To verify whether, in presence of a negative preoperative axillary assessment, SLN can be spared,
- ✓ To verify whether, in presence of a negative preoperative axillary assessment, the decision on adjuvant medical treatment can be taken according only to the biology of the tumour without the prognostic information achieved by SLNB on the nodal status,
- ✓ To verify whether, in presence of a negative preoperative axillary assessment, the patients' quality of life can be improved by a less invasive surgical procedure.

### Primary endpoint

This endpoint, a proxy of overall survival, will allow to have reliable results in a shorter period of time compared to overall survival.

### Secondary endpoint

Secondary endpoints will be the cumulative incidence of distant recurrences, the cumulative incidence of axillary recurrences, the disease free survival (DFS) and the overall survival (OS). Other secondary endpoints are quality of life and evaluation of type of adjuvant treatment administered.

## **PATIENT SELECTION**

### **Eligibility criteria**

- breast cancer  $\leq 2$  cm, and a clinically negative axilla
- any age
- candidates to receive breast conserving surgery + radiotherapy
- negative preoperative assessment of the axilla (ultra-sound with or without FNAC in case one doubtful node is found)
- written informed consent must be signed and dated by the patient and the investigator prior to inclusion.
- patients must be accessible for follow-up.

### **Exclusion criteria**

- synchronous distant metastases
- previous malignancy
- bilateral breast cancer
- multicentric or multifocal breast cancer
- previous primary systemic therapy
- pregnancy or breastfeeding
- pre-operative diagnosis (cytology or histology) of axillary lymph node metastases
- pre-operative radiological evidence of multiple involved or suspicious nodes
- patients with psychiatric, addictive, or any disorder, which compromises ability to give informed consent for participation in this study.

## RANDOMIZATION PROCEDURES

### Randomization procedures

1. Verify eligibility for randomization
2. Obtain written informed consent signed and dated by the patient and investigator after an axillary ultrasound with or without FNAC has been performed.
3. If eligibility criteria are satisfied (negative axillary assessment) the sponsor will provide to the satellite center the UPN (Unique Patient Number).
4. Randomization will be performed using the randomization program (<https://it.tenalea.net/ieo>) .  
After signing on-line with a user name and a password provided by the IEO Division of Epidemiology and Biostatistics answer all of the questions of randomization form. The system will provide you with the randomization date and a patient ID used on all documents to identify the patient. The randomization program will give a treatment assignment (1. SLNB; 2. no axillary surgical staging).

### Information required by randomization program "Tenalea"

- Patient's date of birth
- Patient's initials
- Institution
- UPN (Unique Patient Number) provided by the sponsor

### Randomized group

Randomization to 2 arms:

- SLNB
- no axillary surgical staging

## **DATA MANAGEMENT**

We will conduct the trial according to the ICH Good Clinical Practice (GCP) guidelines. Keeping accurate and consistent records is essential to a cooperative study.

Each case report forms (CRF's) must be filled in by the site investigator or data manager. The site investigator is responsible for CRF completeness.

The methodology of collecting data will be done by software Heavybase. The eCRF system (electronic case report form) is based on a peer to peer system.

This system allows an installation of software in local (on the user's client) enabling users to work offline, without an internet connection.

The system will be automatically update in presence of an internet connection, synchronizing data of all centers, leaving visible for each center records (patient) relevant for the center.

The IEO Data Management Office will be responsible of the study database and data management.

IEO Data Management Office (Senology Division)

[name]

[name]

[contact] or [name]

Email: [[contact]](mailto:[contact])

### **SERIOUS ADVERSE EVENT (SAE)**

A serious adverse event is defined in general as any undesirable medical occurrence that occurs during or within 4 weeks after stopping study treatment that results in any of the following:

- is fatal (any cause)
- life-threatening,
- requires or prolongs hospitalization,
- results in persistent or significant disability/incapacity or
- is a secondary cancer
- requires significant medical intervention

The treatment of the study consists of SLNB vs no axillary surgery. Serious adverse events for this study will include any serious medical condition that occurs after randomization, during surgery or during the 4-week post-surgical period. Furthermore, any death or any serious event that occurs after 4 weeks of surgery, but that is considered to be at least possibly related to the previous surgery should be considered an SAE and reported as such.

Other significant/important medical events, which may jeopardize the patient, or may require significant medical intervention to prevent one of the other serious outcomes listed above, are also considered a serious adverse event.

#### **Reporting Procedures**

All SAEs (irrespective of suspected causation), which occur while the patient is on study must be reported by the investigator to the European Institute of Oncology IEO Data Management Office and within one working day of discovery, using the Serious Adverse Event Report Form.

Serious adverse events must also be reported by the Principal Investigator to the Local Ethic Committee

Regulatory authorities and other investigators, as well as institutional and corporate partners, will be informed by IEO as required by the ICH guidelines and laws and regulations in the countries where the clinical trial is being conducted.

Patients experiencing SAEs should be followed carefully until the condition resolves or stabilizes, and every effort should be made to clarify the underlying cause. Follow-up information related to SAEs must be submitted to the IEO Data Management as soon as relevant data is available, using the SAE Follow-up Report Form.

### TABLE OF TRIAL PARAMETERS

| Visit                                  | 1             | 2              | 3  | 4  | 5  | 6  | 7  | 8  | 9  | 10 | 11 |
|----------------------------------------|---------------|----------------|----|----|----|----|----|----|----|----|----|
|                                        | Random | Surgery |    |    |    |    |    |    |    |    |    |
| Month                                  | 0             | 6              | 12 | 18 | 24 | 30 | 36 | 42 | 48 | 54 | 60 |
| Visit Procedure                 |               |                |    |    |    |    |    |    |    |    |    |
| Check inclusion & exclusion criteria   | x             |                |    |    |    |    |    |    |    |    |    |
| Informed Consent                       | x             |                |    |    |    |    |    |    |    |    |    |
| History                                | x             |                |    |    |    |    |    |    |    |    |    |
| Weight, Height                         | x             |                |    |    |    |    |    |    |    |    |    |
| Physical examination                   | x             | x              | x  | x  | x  | x  | x  | x  | x  | x  | x  |
| Investigations                  |               |                |    |    |    |    |    |    |    |    |    |
| Axillary US                            | x             |                |    |    |    |    |    |    |    |    |    |
| Fnac                                   | m             |                |    |    |    |    |    |    |    |    |    |
| Assessment                      |               |                |    |    |    |    |    |    |    |    |    |
| Quality of life                        | x             | x              | x  | x  | x  | x  | x  | x  | x  | x  | x  |
| x=mandatory
m= if medical indicated |               |                |    |    |    |    |    |    |    |    |    |

## **SAMPLE SIZE CALCULATION AND STATISTICAL CONSIDERATIONS**

Women with pT1 tumours and negative axillary ultrasound will be randomized to receive either SLNB or no treatment in the axilla. We will consider women who will undergo SLNB as the reference group, and we will test for non-inferiority the group of women not undergoing any treatment in the axilla. The primary endpoint will be distant disease free survival (DDFS) after randomization, with distant metastases and deaths from all causes counted as failures.

For the purpose of sample size calculation, the 5-year DDFS in the reference group is assumed to be 96.5%. This estimate was obtained from the analysis of 2218 women with pT1, cN0, M0 tumours who underwent surgery (with SLNB) at the European Institute of Oncology from 01/01/2003 to 31/12/2005.

Overall, 1560 women (780 per arm) will be enrolled to decide whether the group without treatment of the axilla is no worse than the reference group, given a margin  $\Delta$  of non-inferiority of 2.5% (maximum tolerable 5-years DDFS = 94%). Statistical power and one-sided type I error are set to 80% and 5%, respectively.

The accrual period for the experimental study phase will be 5 years, and the additional follow-up years after the last entry will be 5 years. After 3 years from the start of accrual an interim safety analysis will be performed. If the 99% lower confidence bound for the hazard ratio of DDFS is  $> 1.0$ , the trial is stopped and the experimental treatment is declared inferior to the standard treatment (14).

The primary endpoint will be the DDFS, defined as the time free of both distant recurrence and death from any cause. If a patient have simultaneous locoregional and distant recurrences, she will be considered as having a distant recurrence in the analysis. Local recurrences, regional recurrences, contralateral breast cancers and other non-breast primary tumours will be considered as censoring events. The log-rank test will be used to test differences in DDFS. Secondary endpoints will be the cumulative incidence of distant recurrences, the cumulative incidence of axillary recurrences, the disease free survival (DFS) and the overall survival (OS). Differences in the cumulative incidence will be evaluated in a competing risk framework (15) by means of the Gray test (16), while differences in DFS and OS will be evaluated by means of the Log-rank test. Multivariable Cox regression models will be applied to adjust the risk estimates of interest for other variables. The Chi-square test for trend, Chi-square test and the Fisher exact test will be used to evaluate

differences in percentages between the two treatment groups, as appropriate. The T-tests will be used to evaluate differences in means for continuous variables.

All analyses will be carried out with the SAS software (SAS Institute, Cary, NC) and the R software (The R Development Core Team 2004; Free Software Foundation, Boston, MA). All tests will two-sided. The calculation of sample size was carried out using PASS software, based on method given in Jung SH et al. (17).

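### Improved quality of life is a trial aim with a score at eleven visits, but the only stated method that fits is a generic T-test, with no use of baseline and no deciding contrast

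*Supplement*

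**What the plan says.** All protocol references are to the latest version.

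- **Aim.** Trial Objectives lists three aims. The third is to verify whether "the patients' quality of life can be improved by a less invasive surgical procedure". This is a claim of benefit, not of non-inferiority.
- **Endpoint status.** Under Secondary endpoint: "Other secondary endpoints are quality of life and evaluation of type of adjuvant treatment administered".
- **Schedule.** The Table of Trial Parameters has a row "Quality of life" marked mandatory in all eleven columns. The month row reads 0, 6, then "12 | 18 | 24 | 30 | 36 | 42 | 48 | 54 | 60". That is one assessment at randomization and ten afterwards.
- **Method.** Sample Size Calculation and Statistical Considerations does not mention quality of life. For any continuous outcome it says "The T-tests will be used to evaluate differences in means for continuous variables", and on sidedness "All tests will two-sided". Adjustment appears only for time-to-event estimates: "Multivariable Cox regression models will be applied to adjust the risk estimates of interest for other variables".
- **SAP.** Section 1.2 prints the adjuvant-treatment objective twice and has no quality-of-life objective. Section 4.2 does not list quality of life among the secondary outcomes. Sections 5.1 and 5.2 give no method for it. The T-test appears in 5.1 only as a test that will not be applied to baseline characteristics.

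**The concern.** A score taken eleven times per woman can be compared between arms in many ways: at any one visit, as an average, as a change from baseline, or visit by visit. The plan does not say which of these answers the aim. The one test it offers for means uses a single number per woman and, in its plain form, takes no account of where she started.

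Two things are at stake. First, precision: women differ in quality of life before surgery, and that variation stays in the error term unless the month-0 score is used. Second, freedom of choice: with no deciding contrast named, the visit that supports a claim of improvement could be picked after the results are known. Better quality of life is a stated aim of a trial that tolerates up to 2.5 points lower 5-year DDFS, so the evidence for it should rest on a comparison fixed in advance.

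**Working it through.** **The plan's own figure.** No sample size, power or error rate is given for quality of life. The only planning figure is for DDFS: 1560 women, with "Statistical power and one-sided type I error are set to 80% and 5%, respectively". It reproduces:

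- Margin as a hazard ratio: HR = ln 0.94 / ln 0.965 = 1.737, so p = HR/(1+HR) = 0.635.
- Events: (1.645·√(p(1−p)) + 0.842·0.5)² / (p − 0.5)² = 81.2.
- With exponential survival, 5 years' uniform accrual and 5 further years, the event probability at the reference hazard is 0.0520, which gives about 1,562 women.

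This does not bear on the present point, except that it supplies 780 women per arm.

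**Inputs.** Ten post-baseline assessments and one baseline assessment (Table of Trial Parameters); two-sided tests (statistical section). Assumed, because the documents do not give them: a 5% level for quality of life, a roughly continuous score, complete data, and the correlations r shown below.

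**1. Precision at one visit.** Relative to an unadjusted T-test, covariance adjustment for baseline multiplies the variance by 1 − r². A T-test on change from baseline multiplies it by 2(1 − r). The detectable difference at 780 per arm (80% power, two-sided 5%) is (1.960 + 0.842)·√(2/780)·√(factor).

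| r | Unadjusted | Change score | Baseline-adjusted | Cut by adjusting | Detectable difference, adjusted |
|---|---|---|---|---|---|
| 0.3 | 1 | 1.40 | 0.91 | 9% | 0.135 SD |
| 0.5 | 1 | 1.00 | 0.75 | 25% | 0.123 SD |
| 0.7 | 1 | 0.60 | 0.51 | 49% | 0.101 SD |

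The unadjusted detectable difference is 0.142 SD. The ratio of the adjusted to the change-score variance is (1 + r)/2, or 0.65, 0.75 and 0.85 here, so adjustment is the more precise at each of these correlations.

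**2. Averaging the ten visits.** If all pairs of scores correlate at r, the ten-visit mean has variance (1 + 9r)/10 and covariance r with baseline. Its baseline-adjusted variance is (1 + 9r)/10 − r². At r = 0.5 that is 0.55 − 0.25 = 0.30, a standard error √0.30 = 0.55 times that of one unadjusted visit. The expression peaks at r = 0.45 (0.3025), so 0.55 is close to the least favourable ratio under this correlation pattern.

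**3. Error rate if every visit were tested and any significant one counted.** With independent visits: any difference 1 − 0.95¹⁰ = 40.1%; any difference favouring omission 1 − 0.975¹⁰ = 22.4%. The correlated cases come from 400,000 simulated sets of ten standard normal statistics.

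| Between-visit correlation | False 'differs' (nominal 5%) | False 'improved' (nominal 2.5%) |
|---|---|---|
| 0 | 40.1% | 22.4% |
| 0.3 | 35.0% | 17.8% |
| 0.5 | 28.8% | 14.5% |
| 0.7 | 21.2% | 10.6% |
| 0.9 | 12.8% | 6.4% |
| decaying (AR(1)), 0.7 | 30.0% | 15.4% |
| decaying (AR(1)), 0.9 | 18.7% | 9.4% |

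**The case against.** The strongest reply is that the T-test sentence is general boilerplate. The statistical section never names quality of life, and the SAP omits it, so on this view the real gap is an aim with no planned analysis, and the error rates describe an analysis nobody has written down. Much of this stands. The SAP omission is the larger gap, and neither an every-visit rule nor a level for quality of life is stated.

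It does not dispose of the point. Quality of life is the only repeatedly measured, plausibly continuous outcome the sentence can serve, and no other method is offered. Restoring quality of life to the SAP under the protocol's wording would still leave eleven scores, a T-test and no deciding comparison.

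Three stronger readings are tempting and are not supported:

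- *The plan gives ten tests at full alpha.* It says neither that each visit will be tested nor that one will.
- *The baseline score goes unused.* No use is stated, but a T-test on change scores is a difference in means and is not excluded.
- *A false improvement is several times likelier than 5%.* Even under the any-visit rule it is 14.5% at correlation 0.5 and 6.4% at 0.9, that is 2.9 and 1.3 times 5%. The multiple is about 2.6 to 9 only against its own nominal 2.5%.

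It is also fair that the 0.55 ratio compares a five-year average with a single visit. These are different quantities, and a fading effect would shrink along with the standard error.

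**Conclusion.** The point holds as a shortfall in method, and it is a cheap improvement. For a stated aim with eleven mandated assessments, the only fitting method is a generic T-test, with no stated use of baseline, no within-woman correlation and no deciding contrast; the SAP does not fill the gap.

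The precision loss at a single visit, 9% to 49% of the variance for assumed baseline correlation 0.3 to 0.7, applies to an unadjusted T-test and needs no assumption about how many visits are tested. The error inflation, about 13% to 40% for a false difference and 6% to 22% for a false improvement, is conditional on an any-visit rule that the documents leave open. It should be read as the exposure created by silence, not as the error rate of the written plan. Several subscales tested in the same way would raise it further, but no questionnaire is named. The primary DDFS analysis is not affected.

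**What to change.** Add quality of life to the SAP with:

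1. One repeated-measures linear model of the post-baseline scores, with arm, visit, arm-by-visit and month-0 score as terms and correlation between scores from the same woman.
2. One deciding contrast, fixed before the data are seen. An example is the adjusted mean difference averaged over the post-baseline visits, on one pre-named scale of the questionnaire used, tested at two-sided 5% with a 95% confidence interval. This holds a false difference at 5% and a false improvement at 2.5%. Keeping ten visit-level tests would instead need about 0.5% each (0.05/10).
3. Single visits and other scales reported descriptively with confidence intervals.

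The cost is SAP wording and one model. No visits or assessments are needed beyond those the protocol mandates. The sponsor should, however, confirm which questionnaire was used and where its scores were recorded, because none of the six forms in the protocol's Case Report Forms Schedule is a quality-of-life form. The downside is that a benefit confined to early visits is diluted in an average. If that pattern is expected, a different single contrast can be named, provided it is named in advance.

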## **ETHICAL CONSIDERATIONS**

### Patient protection

The responsible investigator will ensure that this study is conducted in agreement with the Declaration of Helsinki.

The protocol has been written, and the study will be conducted according to the ICH Harmonized Tripartite Guideline for Good Clinical Practice (ref: <http://www.ifpma.org/pdfifpma/e6.pdf>).

The protocol will be approved by the Local Ethics Committee.

### Subject identification

A sequential identification number will be automatically attributed to each patients randomized in the trial. This number will identify the patient and must be included on all case report forms. In order to avoid identification errors, patients initials (maximum of 4 letters), and year of birth will also be reported on the case report forms.

### Informed consent

All patients will be informed of the aims of the study, the procedures and possible hazards to which they will be exposed, and the mechanism of treatment allocation. They will be informed as to the strict confidentiality of their patient data, but that their medical records may be reviewed for trial purposes by authorized individuals other than their treating physician. The patients informed consent statement is given at the end of the protocol. It will be emphasized that the participation is voluntary and that the patient is allowed to refuse further participation in the protocol whenever he/she wants. This will not prejudice the patient's subsequent care. Documented informed consent must be obtained for all patients included in the study before they are randomized. The informed consent procedure must conform to the ICH guidelines on Good Clinical Practice. This implies that "the written informed consent form should be signed and personally dated by the patient or by the patient's legally acceptable representative".

Informed Consent and Patient Information Sheet is provided

## ADMINISTRATION RESPONSABILITIES

### The Principal investigator of the study

The Principal investigator of the study will be responsible for writing the protocol, reviewing all case report forms and documenting his/her review on evaluation forms, the contents of the reports, and for publishing the study results. He will also generally be responsible for answering all clinical questions concerning eligibility, treatment, and the evaluation of the patients.

### Trial insurance

European Institute of Oncology as the sponsor of the study, contracts adequate Clinical Trial Insurance, in accordance with all relevant legal requirements

European Institute of Oncology will not provide insurance for the satellite centers which will participate to this trial; every satellite center is requested to provide personal insurance.

